#### Discontinuation phase

The discontinuation phase starts with baseline measurements of thyroid function and secondary outcome parameters (see table 1), followed by a consultation of the participant with their GP during which discontinuation of levothyroxine is initiated, except when TSH level ≥10 mU/L. Levothyroxine is discontinued stepwise, and at intervals of ≥6 weeks to ascertain a steady-state concentration has been reached before the following control visit. This is in line with standard clinical practice. During each ‘6 week’ visit, the GP evaluates thyroid function and symptoms with the participant. On agreement, the daily dose of levothyroxine can then be lowered provided thyroid function is within the predefined limits, that is, a normal fT4 and TSH <10 mU/L. With each step, the dose of levothyroxine is reduced by approximately 25 mcg (the use of whole tablets is preferred) until a daily dose of 25 mcg or less is reached. The GP is free to adjust the size of the dose reduction if necessary. The maximum dose reduction in medication is 50 mcg in the first step. In the final step, the medication is discontinued completely if the laboratory results are still within the predefined limits. The discontinuation phase ends after the evaluation of complete withdrawal of the levothyroxine treatment (ie, 6 weeks after the final discontinuation step). Secondary outcome parameters are collected at the first ‘6 week’ visit and the end of discontinuation (see table 1).

Participants are requested to stop the discontinuation phase when a TSH level ≥10 mU/L or an fT4 level below the normal range is identified during a control visit and is confirmed by an extra thyroid function measurement within 2 weeks. When the extra measurement does not confirm a TSH level ≥10 mU/L or a low fT4 level, the participant is allowed to proceed with the discontinuation phase. Factors other than thyroid function, such as symptoms, may however be a reason to prematurely stop the discontinuation or restart levothyroxine. On stopping the discontinuation phase, it is at the discretion of the physician and the participant to decide whether the dose of levothyroxine at that moment will be maintained or increased. Participants who have stopped the discontinuation phase prematurely will be followed up in accordance with the protocol if possible.

#### Follow-up phase

The follow-up phase ends with a final visit 52 weeks after the start of the discontinuation phase and includes the assessment of thyroid function, current dose of levothyroxine, and secondary outcome parameters (see table 1).

#### Adherence

Participants are contacted by the research nurse by telephone and/or by mail or email prior to each measurement and in case of missing data, to ensure data quality and to promote participant retention and complete follow-up.

### Descriptive study data and outcome measures

Descriptive data recorded at prebaseline include (see online supplemental appendix 2):

10.1136/bmjopen-2022-070741.supp2Supplementary data

Age and sex.Lifestyle: smoking, alcohol intake.Medical history.Complex health problems (Integrated Systematic Care for Older Persons (ISCOPE) questionnaire).^27 28^The participant’s attitude towards deprescribing (revised Patients’ Attitudes Towards Deprescribing (rPATD) questionnaire).^29^Treatment satisfaction for levothyroxine treatment (Treatment Satisfaction Questionnaire for Medication (TSQM)).^30^The participant’s view on what is a substantial dose reduction of levothyroxine (Goal Attainment Score (GAS)).

The primary outcome is the proportion of participants who withdraw their thyroid medication successfully (defined as normal fT4 levels and TSH levels <10 mU/L) at 52 weeks after the start of the discontinuation (final follow-up).

Secondary outcome measures determined at baseline and/or final follow-up include (see online supplemental appendix 2):

Thyroid-related quality of life (ThyPRO-39).^31 32^General health-related quality of life (EuroQol-5D, including the EuroQol visual analogue scale.^33^ Cognitive function is determined as an additional dimension (EuroQol-5D+C).^34 35^Participant’s view on whether they achieved a substantial dose reduction of levothyroxine (Goal Attainment Scale (GAS)).Participant’s view on regret after the decision to withdraw levothyroxine (Decision Regret Scale (DRS)).^36^

To further explore the quality of life during the discontinuation phase, ThyPRO-39 and EuroQol measurements were also determined 6 weeks after the first step of lowering the dose of levothyroxine (T6) and 6 weeks after the last step of dose-lowering (see table 1).

### Sample size calculation

The sample size calculation is based on the primary outcome, the proportion of participants successfully stopping levothyroxine treatment between baseline and final follow-up at 52 weeks. Since population proportions of successful levothyroxine treatment cessation are unknown (the aim of this study), we estimated a proportion of 50% of the participants who successfully discontinue levothyroxine treatment. An estimated proportion of 50% results in the most conservative estimate (resulting in the highest calculated sample size) and is in line with the limited available evidence.^37–39^ We have chosen a sample size of 385 participants because this allows us to estimate the expected proportion of 50% with a 95% CI of which the lower and upper limit is expected to deviate by 5 percentage points from the found percentage (ie, 45% to 55% when the found percentage is indeed 50%).

Taking a maximum of 25% loss to follow-up into account over the duration of 15 months (exclusion at T-12 when TSH level ≥10 mU/L and/or fT4 below reference range, withdrawal, moving away or death between T-12 and T52) a maximum of 513 participants will be recruited. Based on a data query from the academic network of general practices in the region of Leiden, it was estimated that the projected sample size will be reached after inclusion of 53 standard general practices.

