**Methods and analysis:**

Participants are community-dwelling subjects aged ≥60 years using levothyroxine continuously at a stable dosage of ≤150 µg and a level of thyroid-stimulating hormone (TSH) <10 mU/L. After a control period of 12 weeks, levothyroxine treatment is discontinued gradually using a stepwise approach with regular monitoring of thyroid function guided by their GP. The primary outcome is the proportion of participants withdrawn from levothyroxine while maintaining a free T4 level within the reference range and a TSH level <10 mU/L, 52 weeks after the start of discontinuation. Secondary outcomes are compared with the control period (self-controlled) and include among others, the effects on thyroid-specific and general health-related quality of life. Furthermore, patients’ attitudes towards deprescribing and regret regarding discontinuing levothyroxine treatment will be recorded. A total of 513 participants will be recruited to estimate the expected proportion of 50% with a 95% CI ranging from 45% to 55%.

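### The stated 45% to 55% precision treats 385 participants as independent, although they are nested in about 53 GP practices; at a 50% success rate the interval would be modestly wider

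*Protocol article*

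**What the plan says.** The section on sample size calculation rests on the primary outcome, a single proportion. It plans on one half: "we estimated a proportion of 50% of the participants who successfully discontinue levothyroxine treatment". It then fixes the number to be analysed: "We have chosen a sample size of 385 participants because this allows us to estimate the expected proportion of 50% with a 95% CI", where "the lower and upper limit is expected to deviate by 5 percentage points from the found percentage". The only inflation is for attrition: "Taking a maximum of 25% loss to follow-up into account over the duration of 15 months", which leads to the statement that "a maximum of 513 participants will be recruited". The abstract repeats the precision claim: "A total of 513 participants will be recruited to estimate the expected proportion of 50% with a 95% CI ranging from 45% to 55" per cent.

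The same section gives the recruitment base: "the projected sample size will be reached after inclusion of 53 standard general practices". No ICC or design effect appears.

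Several sections describe the GP's part:

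- Study setting: GPs identify eligible patients from their own records and may leave out those they think could be harmed.
- Discontinuation phase: each reduction is agreed between GP and participant, and "The GP is free to adjust the size of the dose reduction if necessary". Symptoms and other non-laboratory factors may lead to stopping early or restarting.
- (Serious) adverse events: when complaints arise, the GP decides whether withdrawal continues or the dose is held or raised.

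The data analysis plan names no confidence interval method for the primary proportion and does not mention practice.

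**The concern.** Estimating this proportion is the primary aim, and the expected interval width is the only quantitative justification given for the sample size. A precision formula for independent observations is right only if two participants from the same practice are no more alike in outcome than two from different practices.

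There are reasons to doubt that here. Success requires both acceptable laboratory values at 52 weeks and being off levothyroxine. The second part depends partly on decisions by the GP, and the GP also shapes who enters. Practices that select or taper differently would have different success rates, which is what a positive ICC means.

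Two things are at stake. The published expectation of 45% to 55% may be somewhat optimistic. And if the reported interval ignored practice, it would overstate how well the proportion is known.

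**Working it through.** **Inputs from the protocol article.** Proportion 0.50, half-width 0.05, 95% confidence, 385 analysed, 25% loss, 513 recruited and 53 practices (all from the sample size calculation).

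**Inputs that are assumptions.** The ICC is taken as 0.01, 0.05 or 0.10. Practice sizes are taken as equal, with a variant for unequal sizes. The article gives neither an ICC nor a spread of practice sizes.

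**Step 1: reproduce the plan's figures.**

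- n = 1.96² × 0.50 × 0.50 / 0.05² = 384.15, rounded up to 385.
- Half-width at 385: 1.96 × √(0.25/385) = 4.99 points.
- Recruitment: 385 / 0.75 = 513.3, stated as 513.

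Both figures reproduce. The formula contains no term for clustering.

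**Step 2: slack.** 385 / 384.15 = 1.002, so the design effect may not exceed about 1.002 if 5 points are to hold at 50%. With the practice size in step 3 this allows an ICC of only about 0.002 / 6.26 = 0.0004. In effect, any positive ICC exceeds it.

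**Step 3: practice size.** m = 385 / 53 = 7.26 analysed per practice, taking 53 as the number that yields the full sample.

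**Step 4: design effect, half-width and coverage.** DE = 1 + (m − 1) × ICC. Half-width = 1.96 × √(0.25 × DE / 385). If the interval were computed as a simple binomial one, its actual coverage would be about 2Φ(1.96/√DE) − 1.

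| Assumed ICC | DE | Effective n | Half-width at 50% | Coverage of a simple binomial 95% CI |
|---|---|---|---|---|
| 0.01 | 1.06 | 362 | 5.15 points | 94.3% |
| 0.05 | 1.31 | 293 | 5.72 points | 91.3% |
| 0.10 | 1.63 | 237 | 6.37 points | 87.6% |

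**Step 5: sensitivity.**

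- *Unequal practice sizes.* DE = 1 + ((1 + CV²) × m − 1) × ICC. With an assumed CV of 0.65 the half-widths are 5.22, 6.05 and 6.94 points at ICC 0.01, 0.05 and 0.10.
- *Proportion away from 50%.* At 37%, the figure from the meta-analysis cited in the Introduction, the half-width is 4.97 points at ICC 0.01 and 5.53 at 0.05. At 25% it is 4.96 points even at ICC 0.05.
- *Less attrition.* If all 513 were analysed, m = 513 / 53 = 9.68, and the half-width at 50% is 4.5 points at ICC 0.01 and 5.2 at 0.05.
- *What 53 refers to.* The article does not say whether 53 practices yield 385 or 513 recruits. If 385, then 7.26 are recruited per practice and 7.26 × 0.75 = 5.45 analysed. DE at ICC 0.05 is 1 + 4.45 × 0.05 = 1.22, and the half-width is 4.99 × √1.22 = 5.5 points.

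**The case against.** The strongest reply has four parts.

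1. *The endpoint is biochemical and the rules are shared.* Every reduction is tied to the same fT4 and TSH limits, there is a nominal step size, and stopping on laboratory grounds needs a confirmatory test. This stands in part: shared rules limit variation between practices and argue for a small ICC. They do not remove it, because being off treatment still depends on decisions by GP and participant within those limits.

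2. *The size rests on an ICC that the article does not give.* This stands. The figures above are scenarios, and at ICC 0.01 the difference is about 0.2 points. A reader might infer that the 45% to 55% interval will certainly be missed. The article does not support that: 50% is the least favourable proportion, 25% is described as a maximum loss, and 53 practices is a planning estimate.

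3. *The interval method belongs in the statistical analysis plan.* This stands. A reader might infer that a simple binomial interval is planned. The article commits to no method and says that an analysis plan will be made available, so the coverage figures apply only if such an interval is used. The finding is the precision that the article itself states, and that is not deferred.

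4. *No decision depends on exactly 5 points.* True, and it keeps the point from being critical. But the width is the stated reason for 385, so it should match the design.

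A reader might also infer that the logistic models would give standard errors that are too small for practice-related factors. The article names no practice-level predictor, and its listed descriptive variables are all at participant level, so that does not form part of this point.

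**Conclusion.** The point holds as an unstated design assumption, not as an arithmetic error: 385 and 513 both follow from the formula used. That formula assumes independence and leaves no slack, while recruitment and treatment run through about 53 practices. At the planned 50% with 385 analysed, the half-width would be about 5.2 points at ICC 0.01, 5.7 at 0.05 and 6.4 at 0.10, against the stated 5. This rests on assumed ICCs, equal practice sizes and about 7.3 analysed per practice.

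The loss is modest because practices contribute few participants each, and a proportion well away from 50% or lower attrition could absorb some or all of it. If a simple binomial interval were used, coverage would fall to about 94% at ICC 0.01 and 91% at ICC 0.05. The change is worth making because it is cheap and concerns the trial's headline interval; it does not threaten the trial.

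**What to change.** - Keep the recruitment target of 513.
- In the sample size section, and wherever the 45% to 55% range is repeated, state that it assumes independent participants. Add the expected precision under a stated ICC: about 5.2 to 5.7 points for ICC 0.01 to 0.05, with 6.4 points at 0.10 as an upper scenario. Say whether 53 practices refers to 385 or 513 participants.
- In the statistical analysis plan, if it does not already do so, compute the primary 95% confidence interval with a method robust to clustering by practice. Examples are GEE with practice as the cluster, or a Wilson interval adjusted for the design effect. Report the observed ICC with it.

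The cost is wording and one analysis option, with no extra participants. The stated precision becomes slightly less favourable and the reported interval slightly wider. Holding 5 points at 50% by enlarging the sample would take about 505 analysed at ICC 0.05 (384.15 × 1.313), or about 674 recruited (505 / 0.75). That is hard to justify for a gain of about 0.7 points.

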### Data analysis plan

GPs transfer participants’ data after each visit using a validated electronic data capture (EDC) system (Castor EDC). Questionnaires are completed on paper or electronically (Castor EDC). All participant data are coded. Only the principal investigators and the research team have access to the key to these codes. The handling of personal data complies with the European General Data Protection Regulation. Database validation checks are run routinely and are tracked and escalated as appropriate.

To determine the proportion of the population that can be withdrawn from levothyroxine treatment, categorical data involving measurements at baseline and final follow-up will be analysed. Univariable and multivariable logistic regression analyses will be performed to assess factors that are associated with successful discontinuation of levothyroxine treatment. To estimate the effect of discontinuation on secondary outcome parameters measured at baseline and/or final follow-up, descriptive, univariable and multivariable analyses will be performed for the overall group and for the group of participants who successfully discontinued levothyroxine. Measurements pre and post discontinuation will be compared. Variations in thyroid function, thyroid-related quality of life, treatment satisfaction for levothyroxine, general health and participant’s attitude towards deprescribing will be determined using prebaseline and baseline measurements. All analyses will be carried out with the population of participants who enrolled at baseline (T0). Participants who experience intercurrent events not related to the study procedure resulting in missing data at final follow-up will be excluded. Primary and secondary analyses will be repeated with all participants who enrolled at baseline who have data for the outcome variable of interest and have had their final follow-up visit. Statistical significance for the primary outcome requires p ≤0.05.

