Treatment with levothyroxine for both overt and subclinical hypothyroidism, is often continued for life, as current guidelines do not advise re-evaluation of the indication and effect.^8 14^ Initial indications for treatment are not always well documented and can be inaccurate or even inappropriate.^15^ Patients may have started levothyroxine in the past for a diagnosis made during transient hypothyroidism.^15–17^ Furthermore, thyroid (dys-)function varies over time,^18^ and thyroid metabolism changes with age.^19^ Therefore, it is likely that a considerable proportion of older adults are treated with levothyroxine without a clear indication according to current guidelines. This could be harmful, considering that oversuppression (TSH <0.45 mU/L) has been reported in 41% of older levothyroxine users^20^ and increases the risk of bone fractures and atrial fibrillation.^21 22^ The risk of oversuppression increases with treatment duration^8^ and although guidelines warrant careful medication monitoring, levothyroxine dosages may remain unchanged for a long time.^23^

Taking into account the high levothyroxine use in older age, the controversy regarding treatment of subclinical hypothyroidism, the lack of re-evaluation of indications, and the health risks associated with oversuppression, it can be hypothesised that discontinuation of levothyroxine treatment can be achieved without negative consequences for a considerable proportion of older adults. A meta-analysis based on observational studies including participants aged 2–81 years suggested that approximately 37% remain euthyroid after thyroid hormone discontinuation.^24^ However, the evidence was of low quality, the adult participants were mostly middle-aged, and no study followed a systematic approach for deprescribing levothyroxine.

Therefore, the primary aim of this self-controlled trial is to investigate what proportion of community-dwelling levothyroxine users aged 60 years and older can withdraw from levothyroxine treatment successfully. Secondary aims are as follows: (1) to study what proportion of participants can achieve a substantial dose reduction of levothyroxine at 52 weeks (a) defined as ≥50% and (b) defined by the participants themselves; (2) to study the effect of discontinuation of levothyroxine treatment at 52 weeks on (a) thyroid-related quality of life and (b) general health; (3) to determine how participants reflect on their decision to discontinue levothyroxine treatment.

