## Methods

### Study design

This is a self-controlled trial investigating the stepwise discontinuation of levothyroxine treatment in adults aged 60 years and older with a follow-up of 1 year. Outcomes will be measured 12 weeks before the start of discontinuation, at the start of discontinuation, at 6 weeks, at the end of discontinuation and after 52 weeks. The outcomes will be compared within participants. In this way, the research questions can be studied validly in a self-controlled design, without the need for an extra control group. The formal role of a control group in a randomised trial is to estimate what would have happened in the experimental arm in the absence of the intervention.^25^ This effect is immediately clear in our study: levothyroxine treatment is simply continued in almost all patients. Therefore, a control group in our study will only reveal information that is already known.^26^ The primary outcome of the study is based on a biochemically defined thyroid function status, an fT4 level within the reference range and a TSH level <10 mU/L. Since this biochemically defined outcome is independent of participants’ views or experiences, is not influenced by personal interpretation and is therefore not affected by an unblinded design, we considered a control group as not required. A TSH level of <10 mU/L was based on the results from the recently published randomised clinical trials on levothyroxine treatment in older adults with subclinical hypothyroidism.^11–13^

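### The week-52 quality-of-life effect is tied to baseline and final follow-up, so people without a T52 score have no stated way to contribute their T6 and end-of-taper scores

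*Protocol article*

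**What the plan says.** The Introduction sets the secondary aim: "to study the effect of discontinuation of levothyroxine treatment at 52 weeks on (a) thyroid-related quality of life and (b) general health".

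The Study design section gives the measurement plan: "Outcomes will be measured 12 weeks before the start of discontinuation, at the start of discontinuation, at 6 weeks, at the end of discontinuation". The last occasion is week 52. Table 1 marks ThyPRO-39 and the EuroQol VAS at all five occasions.

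The Data analysis plan then describes the effect analysis: "To estimate the effect of discontinuation on secondary outcome parameters measured at baseline and/or final follow-up, descriptive, univariable and multivariable analyses will be performed". This is done in the whole cohort and in the subset who stopped successfully. The section adds: "Measurements pre and post discontinuation will be compared". It gives the T-12 scores a use, namely natural variation together with T0. It names no analysis for T6 or the end of the taper. Those two occasions are explained only under Descriptive study data and outcome measures: "To further explore the quality of life during the discontinuation phase, ThyPRO-39 and EuroQol measurements were also determined 6 weeks after the first step". The same sentence covers the score taken after the last step.

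Two populations are defined. The main one is everyone enrolled at T0, minus those whose final data are missing because of intercurrent events unrelated to the study procedure. The repeat analysis takes those "who enrolled at baseline who have data for the outcome variable of interest and have had their final follow-up visit".

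**The concern.** A T0-to-T52 change cannot be computed without a T52 score. The main population nominally keeps people who left for study-related reasons, but the plan gives their missing score no treatment. For the primary outcome such a person could be counted as not successfully withdrawn; a questionnaire score has no such default. People lost through unrelated events are removed from the main analysis, and the repeat analysis requires a final visit. In each case, T6 or end-of-taper scores already in the database do not inform the week-52 estimate.

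The protocol itself makes selective loss plausible. It acknowledges that the unblinded design may bias the secondary endpoints, accepts symptoms as a reason to end the taper, and lets participants withdraw without giving a reason. That last point also makes it hard to classify a loss as unrelated. At stake is the evidence on whether stopping is well tolerated, which the Introduction's hypothesis relies on.

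**Working it through.** **The plan's own figures.** The only stated sample-size figures concern the primary proportion. They reproduce: 1.96² × 0.5 × 0.5 / 0.05² = 384.15, rounded up to 385; and 385 / 0.75 = 513.3, against 513 stated. The protocol gives no SD, correlation or dropout-by-score figure for quality of life, so everything below rests on assumptions.

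**Bound on loss.** "Taking a maximum of 25% loss to follow-up into account over the duration of 15 months" also covers exclusions at T-12. If that maximum holds, loss after T0 is below 25%.

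**Algebra.** Let d be the share without T52, and μc and μd the mean worsening in completers and dropouts. The full mean is (1 − d)μc + dμd, so the completers' estimate is off by μc − [(1 − d)μc + dμd] = −d(μd − μc).

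| μd − μc | d = 10% | d = 25% |
|---|---|---|
| 0.25 SD | −0.025 SD | −0.0625 SD |
| 0.50 SD | −0.05 SD | −0.125 SD |
| 0 | 0 | 0 |
| −0.25 SD | +0.025 SD | +0.0625 SD |

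A negative entry means that worsening is understated.

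**Large-sample check.** Assumptions: four visits (T0, T6, end of taper, T52), score SD 1, equal between-visit correlation of 0.5 or 0.7, and true worsening of 0.20 SD at T52. Dropout depends on the change from T0 to the end of the taper, with log-odds per score SD of that change.

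| Who leaves more often (log-odds) | Completers, 10% lost | Completers, 25% lost | All visits |
|---|---|---|---|
| Worse scorers (0.5 to 1.0) | 0.155 to 0.185 | 0.095 to 0.165 | 0.20 |
| Unrelated (0) | 0.20 | 0.20 | 0.20 |
| Better scorers (−0.5) | 0.215 to 0.225 | 0.237 to 0.26 | 0.20 |

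**Trial-size check.** Assumptions: 480 people at T0, correlation 0.5 to 0.7, 10% to 20% missing at T52, and log-odds of 0.5 to 1.0 per SD of the T0-to-end-of-taper change.

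- The completers' bias is about 0.02 to 0.09 SD in the favourable direction, or about 0.5 to 1.8 standard errors (empirical SE 0.037 to 0.052).
- Coverage of the 95% CI is about 58% to 93%. Values near 60% need both 20% missing and log-odds of 1.0; at 0.5, coverage is roughly 85% to 93%.
- The estimate from all four visits has a bias of at most 0.003 SD when every dropout has an end-of-taper score.
- That advantage shrinks when dropouts also lack the end-of-taper score. The remaining bias is about 0.002 to 0.015 SD if half of them lack it, and about 0.006 to 0.03 SD if all do.
- If dropout is unrelated to change, both estimates are unbiased, and the all-visits SE is about 1% to 4% smaller.

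**The case against.** The strongest objection is that the article names no model. Its baseline and/or final follow-up wording also labels the list of secondary outcomes, so it may identify those outcomes rather than limit the visits that enter a model. The word post is not defined as T52 alone. The choice of longitudinal model and the handling of missing scores are normally left to the SAP, which the protocol says will be made available. This stands in part: the absence of a named model is not the point here. What remains is that the article does fix time points and populations, and a SAP that follows them as written carries the limitation over.

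A reader might infer three stronger things, which the document does not support:

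- **That the effect is estimated only in people with a week-52 visit.** That restriction belongs to the repeat analysis. The main population keeps T0 enrollees whose loss relates to the study procedure; what is missing is a route for their scores into the change estimate.
- **That the interim scores are thrown away.** They have a stated exploratory purpose.
- **That worsening is understated as a matter of fact.** This needs those who worsen to leave more often, and the document has no data on it. People who stop the taper early are followed to week 52 where possible, so stopping the taper is not dropout.

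It is also fair to say that a simulation in which dropout depends only on an observed score favours the repeated-measures model by construction. The residual bias when that score is missing is therefore given above.

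**Conclusion.** The point holds in a limited form. As worded, the week-52 effect on ThyPRO-39 and EuroQol rests on a baseline-to-final comparison that does not use T6 or end-of-taper scores, and people without T52 have no stated way to contribute. The consequence is conditional: worsening is understated by about 0.02 to 0.09 SD under the assumptions shown, by nothing if loss is unrelated to change, and it is overstated if improvers leave more often. Using all visits reduces the bias in either direction, so the recommendation does not depend on guessing who leaves. The primary proportion is untouched. This is a cheap improvement of low-to-moderate severity.

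**What to change.** In the Data analysis plan, state that the T52-minus-T0 change in ThyPRO-39 and EuroQol is estimated from a linear mixed model for repeated measures. It should include everyone enrolled at T0, take all collected visits (T-12, T0, T6, end of discontinuation, T52) as visit categories, and allow for within-participant correlation. The exclusion for unrelated events and the requirement of a final visit should not apply to this analysis. Keep the completers' comparison as a sensitivity analysis.

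The cost is a sentence or two in the plan and a standard model, with no new data. There are three downsides. The model assumes that missingness is explained by the observed scores. Some bias remains where dropouts also lack the end-of-taper score. And because the end of the taper falls anywhere from 6 to 36 weeks, it must enter as a visit category rather than at a fixed time, with a rule for one-step tapers, where it coincides with T6.

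### T0 participants with missing week-52 data judged unrelated to the study are dropped from the primary proportion, and the stated repeat analysis cannot show what that does

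*Protocol article*

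**What the plan says.** In the protocol article, the Data analysis plan sets the population for all analyses as the participants enrolled at baseline (T0). The next sentence qualifies this: "Participants who experience intercurrent events not related to the study procedure resulting in missing data at final follow-up will be excluded". One repeat analysis follows: "Primary and secondary analyses will be repeated with all participants who enrolled at baseline who have data for the outcome variable of interest", with the further condition that the final visit took place.

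Other sections bear on how the rule would work:

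- Withdrawal: a participant may leave without giving a reason.
- Discontinuation phase: participants who stop tapering early are followed as planned only where that can be done.
- Strengths and limitations: the study is unblinded. Study design: there is no separate control group.
- Sample size calculation: the loss allowance is given as "Taking a maximum of 25% loss to follow-up into account over the duration of 15 months", and it covers "exclusion at T-12 when TSH level ≥10 mU/L and/or fT4 below reference range, withdrawal, moving away or death between T-12 and T52".

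**The concern.** The primary result is a single proportion. With no comparison arm, selective loss cannot cancel and passes straight into the estimate.

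The exclusion depends on a judgement about cause that can only be made once the data are missing, by people who know how the taper was going. For someone who leaves without a reason, there may be nothing to base it on. The article argues that a biochemical endpoint is safe from the unblinded design. That argument covers how the endpoint is measured. It does not cover the decision about who stays in the denominator.

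Loss is also plausibly linked to failure, because those who stop tapering early have the weaker guarantee of follow-up. If some of them are classed as unrelated losses, the proportion moves upward. The repeat analysis leaves out the same people, so agreement between the two results would say nothing about them.

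**Working it through.** **1. The plan's own figures.** The inputs are an expected proportion of 50% and a "95% CI of which the lower and upper limit is expected to deviate by 5 percentage points from the found percentage" (Sample size calculation).

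n = 1.96² × 0.5 × 0.5 / 0.05² = 384.2, rounded up to 385. This matches "We have chosen a sample size of 385 participants". The half-width at 385 is 1.96 × √(0.25/385) = 4.99 points. Inflation gives 385/0.75 = 513.3, which matches "a maximum of 513 participants will be recruited". Both figures reproduce.

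**2. Who is in each analysis.**

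| T0 participant | Main analysis | Repeat analysis |
|---|---|---|
| Week-52 outcome present, final visit held | in | in |
| Missing, judged related | appears to stay in; how counted is not stated | out |
| Missing, judged unrelated | out | out |

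The last row has no outcome in either analysis.

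**3. Size of the bias.** Let m be the share of the T0 set with a missing outcome, p the success proportion among those observed, and q the success proportion among the missing. The all-T0 proportion is (1 − m)p + mq. If every missing case is excluded, the estimate is p, and the bias is p − [(1 − m)p + mq] = m(p − q). The documents give neither m nor q, so both are assumptions. With p = 50%:

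- q = 30%: 0.10 × 20 = 2 points; 0.20 × 20 = 4 points; 0.25 × 20 = 5 points.
- q = 20%: 0.167 × 30 = 5 points.
- q = 0: 0.10 × 50 = 5 points.

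**4. Against the plan's loss allowance.** The allowance is 513 − 385 = 128 participants, but it also covers losses before T0, which do not bias a T0-based proportion. With 385 observed at 50% (192.5 successes) and the rest of the T0 set missing:

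| T0 set | Missing | m | All missing fail to all succeed | Bias at q = 30% |
|---|---|---|---|---|
| 513 | 128 | 25.0% | 37.5% to 62.5% | 5.0 |
| 487 | 102 | 20.9% | 39.5% to 60.5% | 4.2 |
| 462 | 77 | 16.7% | 41.7% to 58.3% | 3.3 |
| 436 | 51 | 11.7% | 44.2% to 55.8% | 2.3 |
| 410 | 25 | 6.1% | 47.0% to 53.0% | 1.2 |

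Even at q = 0, an upward bias of 5 points needs m of at least 10%, so a T0 set of at least 385/0.9 = 428. It is out of reach once more than about 513 − 428 = 85 of the 128 losses fall before T0.

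**5. When only some missing cases are judged unrelated.** Take the T0 set of 462, with half of the 77 missing (38.5) excluded and the other half kept and counted as failures. That counting is an assumption, since the article does not state the rule. The main estimate is 192.5/(462 − 38.5) = 45.5%, and the repeat gives 50%. If the excluded half succeed at 30%, the all-T0 value is (192.5 + 11.55)/462 = 44.2%, so 1.3 points of bias remain. If none of them succeed, it is 41.7%, and 3.8 points remain. The gap between 45.5% and 50% comes from the related cases and tells the reader nothing about the excluded ones.

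**6. Effect on the interval.** With a standard error of √(0.25/385) = 2.55 points, a bias of 2 points lowers the coverage of a nominal 95% interval to about 88%, and a bias of 5 points to about 50%.

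**The case against.** The best defence is that the rule is narrow. It removes only unrelated losses, such as moving away, where a link to success is weakest. A participant who resumes levothyroxine would hardly be classed as unrelated. The plan also works against loss: a research nurse contacts participants before each measurement and when data are missing, and the final visit records the current dose, so anyone who resumes and attends is seen as a non-success. An analysis plan that is not shown may add sensitivity analyses.

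Much of this stands, and it rules out several stronger readings that a reader might infer:

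- **That both analyses are complete-case.** On the natural reading, related missing cases stay in the main analysis, so the two results can differ.
- **That 25% of the T0 set will be missing, or that a 5-point bias is to be expected.** The 25% is a maximum and includes losses before T0.
- **That the bias must be upward.** It is upward only if the excluded succeed less often than the observed. This is plausible but not shown.
- **That week-52 treatment status is already known for everyone.** GPs transfer data after each visit. Nothing shows that status can be obtained after withdrawal of consent, a move or a death.

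The defence does not reach the rule itself. The article fixes the exclusion, the classification has to be made with incomplete information, and the stated check leaves out the people in question. How a death is counted is a choice of estimand, but it should be made openly and not by dropping the participant.

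**Conclusion.** The point holds in a limited form and should be fixed, though it does not undermine the design. T0 participants whose missing week-52 data are judged unrelated have no outcome in any analysis the article states, so the effect of excluding them cannot be seen.

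The likely size is a few points, not a set figure: 2 to 4 points if 10% to 20% are missing after T0, all are excluded, and 30% of them succeed against 50% of those observed. A bias equal to the planned half-width needs harsher conditions, such as 10% missing with no successes or 25% missing with 30% success. If the excluded losses are truly unrelated, or only some missing cases are excluded, the bias is smaller and may be negligible.

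**What to change.** 1. Delete the exclusion for the primary proportion and keep every T0 participant in the denominator.
2. Count as non-success anyone shown to be back on levothyroxine at week 52, from data already collected or from GP records where consent allows. The Abstract defines success as being withdrawn from the drug, so missing laboratory values do not matter for these participants.
3. For those whose status stays unknown, state the rule in advance. Multiple imputation from last TSH, fT4, dose and step reached is an option, not a requirement.
4. Replace the complete-case repeat with an all-T0 analysis counting missing as non-success (which is also the worst-case bound), and add the best-case bound. Show complete cases as a supplement.
5. If the exclusion is kept for any analysis, fix in advance the criteria for relatedness, who applies them, and how a withdrawal without a stated reason is classed.

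The cost is a little more analysis work, a look-up in GP records where permitted, and possibly a slightly lower reported proportion. No extra participants or visits are needed, and the figures of 385 and 513 do not change.
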